#### 3.6.1. Primary Outcomes

Inspiratory muscle strength is the primary outcome of the study. Maximal inspiratory pressure (MIP) will be used as an indicator of overall inspiratory muscle strength, reflecting the maximum static pressure generated against an obstructed airway. This measure has been chosen for its clinical relevance in identifying diaphragmatic weakness and monitoring adaptations induced by training [34]. The ATS/ERS guidelines recommend performing 3 measurement attempts. According to them, an absolute maximum inspiratory pressure value at the mouthpiece of 80 cmH_2_O usually excludes clinically significant weakness of the inspiratory muscles. In older ages, the limit for men is 60 cm H_2_O and for women, it is 40 cmH_2_O [34]. The measurement of maximum expiratory pressure will be performed using the same equipment, measures the strength of the expiratory muscles and is performed with the patient in a sitting position and closed nose. A maximal inspiratory effort is commanded for 1–2 s and repeated 3–8 times. In women, the normal limit is 120 cmH_2_O of mercury, while in men, it is 150 cm of mercury [35]. In addition, maximal dynamic inspiratory pressure will be assessed using the S-index. The S-index is a new non-invasive method for the dynamic assessment of inspiratory muscle strength. The measurement is performed using an electronic inspiratory muscle training device that applies conical flow resistance as a loading method. The measurement includes 10 maneuvers, with the participant being encouraged to make a maximum effort up to the total lung capacity. At the beginning of the measurement, a warm-up session (one set of 30 breaths at 40% of S-index) has been included to enhance pulmonary function and attenuate the ‘learning effect’ of repeated measurements [27]. This outcome provides information on inspiratory muscle performance under conditions that more closely resemble functional breathing tasks and may be more sensitive to training-related changes than static measurements alone [27,36]. The average value of the S index in healthy populations is 159 cmH_2_O in men and 115.29 cmH_2_O in women [28].

#### 3.6.2. Secondary Outcomes

The severity of GERD symptoms will be assessed using the Reflux Disease Questionnaire (RDQ), a patient-reported outcome measure that records the frequency and intensity of symptoms such as retrosternal heartburn and pain, upper stomach heartburn and pain, sour taste in the mouth, and regurgitation, which are associated with central reflux. The RDQ has been selected based on dyspepsia guidelines for its established use in clinical research to aid in diagnosis (sensitivity 88.1% and specificity 29.8%) [31]. It has been previously validated in Greek-speaking populations with high overall internal consistency (alpha value: 0.91) on three factors related to heartburn, regurgitation, and dyspepsia [29].

Health-related quality of life, specifically related to GERD, will be assessed with the Short Form Regurgitation Quality Questionnaire (RQS) [33]. This tool assesses the impact of reflux symptoms on daily activities (4 questions), psychological well-being (2 questions), sleep and eating behavior (2 questions), thus providing an insight into the broader consequences of symptom change beyond physiological measures [33]. The questions are scored on a 5-point scale, and the mean value ranges from 0 (low) to 100 (high). Its validation in the Greek population has been performed by Georganta et al. 2002 showing high internal consistency and validity with that of the sph-36 questionnaire (r > 0.40, *p* < 0.05) [32].

Pulmonary function will be assessed using spirometry, with particular emphasis on the FEV1/FVC ratio, with the main aim of the study being to determine whether or not undiagnosed lung disease is present, expressed as a percentage of predicted values. This procedure will be conducted in accordance with the guidelines proposed by Knudson, Slatin, Lebowitz, and Burrows (1976) [37]. Internal validity will be ensured by calibrating the device before each measurement using a flow–volume syringe. The duration of each subject’s attempt will be 6 s and the best recording will be made after completing at least three acceptable attempts [37,38].

### 3.7. Interventions

An informative session on diaphragmatic breathing with simulated inspiratory muscle exercise after randomization will be given to participants of both groups. This will enhance the role of physiotherapy, specifically the development of a trusting relationship between therapist and participant, increasing their self-confidence [39]. The long-term goals of managing the underlying disease and the health belief model will determine the structure of the session [40].

Intervention group: Participants allocated to the intervention group will follow a 12-week inspiratory muscle training program consisting of three 15 min sessions per week in the morning or afternoon 2 h after breakfast or lunch [41]. Training will be performed using an electronic inspiratory muscle trainer that provides a tapered flow of load resistance, initially at 40% of each participant’s MIP performing 30 breaths per session with 1 set of 30 repetitions [24,42]. Resistance will be progressively increased on a weekly basis at a rate of 10% of the initial maximal inspiratory pressure measurement if patients at the end of the week experience difficulty 3–4 on the Borg scale [43]. Otherwise, the resistance will remain the same. Resistance will also be maintained if the participants present persistent reflux symptoms.

Control group: Participants assigned to the control group will perform sham inspiratory muscle training using the same device with a constant minimal resistance 7 cmH_2_O [23].

A training diary will be kept for all participants that will include all information on the progression of training, missed sessions (along with the reason) and monitoring of their symptoms and medication.

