### 3.6. Outcome Measurements

The outcome assessments have been selected to capture both physiological changes in inspiratory muscle performance as well as clinically significant effects on the severity and frequency of GERD symptoms. A trained physiotherapist will perform: (a) MIP (Micro RPM), according to ERS statement [25,26], (b) S-index measurement (Powerbreathe K5) [27,28] and will administer the Reflux Disease Questionnaire [29,30,31] and Reflux-Qual Short Form Questionnaire [32,33]. All measurements will be performed in random order.

Respiratory function will be assessed with the measurement of FEV1/FVC% using the Spirolab iii spirometer (Medical International Research, Inc., Rome, Italy). This will be performed by a pulmonologist with adequate training.

All measurements will be performed at three pre-specified time points: at baseline (T1), immediately after completion of the 12-week intervention (T2), and at the six-month follow-up (T3) (Table 1).

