## 5. Ethics and Dissemination

This study received ethical approval from the Ethics Committee of the University of West Attica (protocol number 7889-08/02/2024). No further modifications are allowed, as the study has already been revised and approved in accordance with the recommendations of the Ethics and Conduct Committee of the University of West Attica. The trial will be conducted in accordance with the Declaration of Helsinki. The confidentiality of participants will be maintained throughout the study using coded identifiers and access to data will be limited to the research team.

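### As worded, the Borg 3–4 trigger holds the training load for participants who rate it below 3, exactly as for those who rate it above 4

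*Protocol article*

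**What the plan says.** The rule is in section 3.7 (Interventions) of the protocol article. Training starts at 40% of the participant's MIP, three sessions a week for 12 weeks, "performing 30 breaths per session with 1 set of 30 repetitions".

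- **Step:** "Resistance will be progressively increased on a weekly basis at a rate of 10% of the initial maximal inspiratory pressure measurement".
- **Trigger:** "if patients at the end of the week experience difficulty 3–4 on the Borg scale".
- **Default:** "Otherwise, the resistance will remain the same".
- **Further hold:** "Resistance will also be maintained if the participants present persistent reflux symptoms".

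Section 3.6 fixes when MIP is measured: "All measurements will be performed at three pre-specified time points", namely baseline, the end of the 12 weeks, and the six-month follow-up. Section 5 adds: "No further modifications are allowed, as the study has already been revised and approved".

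**The concern.** A progression rule based on perceived effort would normally raise the load when the current one is tolerated. Here the trigger is a closed band, with no words such as 'or below', followed by a default that keeps the load unchanged. Taken at face value, the participant with most reserve (rating below 3) and the participant at the limit (rating above 4) get the same instruction. Only the middle band moves up.

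This works against the weekly progression that the same sentence announces. At stake is the dose delivered in the experimental arm, and through it the size of the effect on the two primary outcomes, MIP and S-index. A therapist who follows the text holds back a participant who could train harder. One who progresses that participant departs from the text.

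**Working it through.** The plan states no figure to reproduce here, so the check is to apply the rule as written.

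**Inputs from section 3.7:** start 40% of initial MIP; step 10% of initial MIP; trigger Borg 3–4; otherwise hold; 12 weeks × 3 sessions = 36 sessions.

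**Assumptions, not in the article:** baseline MIP of 60, 80 or 100 cmH2O; MIP gains of 10, 20 or 30%; a Borg version that has ratings below 3 (the version is not named).

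**1. The rule by rating, without persistent reflux symptoms**

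| End-of-week rating | As worded | Trigger at 4 or less |
|---|---|---|
| below 3 | hold | +10% of initial MIP |
| 3–4 | +10% of initial MIP | +10% of initial MIP |
| above 4 | hold | hold |

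Run week by week, a constant rating of 1 or 2 leaves the load at 40% of initial MIP in all 12 weeks. So does a constant rating of 5 or 7. A rating of 3 or 4 gives 40%, 50%, 60% and so on for as long as it lasts. Setting the trigger at 4 or less changes only the first row.

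**2. Size at the first weekly decision**

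- Held: 40% of baseline MIP. Progressed: 40 + 10 = 50%.
- Withheld step relative to the starting load: 10 / 40 = 25%.
- At an assumed MIP of 60/80/100 cmH2O: held 24/32/40, progressed 30/40/50 cmH2O.

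**3. Relative intensity if MIP rises while the load is held**

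Load as a share of current MIP = load as a share of baseline MIP / (1 + gain).

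| Assumed MIP gain | Held at 40% | After one step (50%) |
|---|---|---|
| 10% | 40/1.1 = 36.4% | 50/1.1 = 45.5% |
| 20% | 40/1.2 = 33.3% | 50/1.2 = 41.7% |
| 30% | 40/1.3 = 30.8% | 50/1.3 = 38.5% |

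A single step keeps relative intensity at or above the starting 40% for gains up to 50/40 − 1 = 25%.

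**4. Is there another route to a higher load?**

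None is written. The symptom rule is a second reason to hold. Steps are scaled to initial MIP, and section 3.6 schedules no MIP measurement between baseline and the end of training that could reset the load. A later rating of 3–4 would restart progression, but at a fixed load a participant who gets stronger has no evident reason to rate it harder.

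**5. What cannot be computed**

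The article gives neither the frequency of ratings below 3 nor a dose-response for load. The effect on the between-group difference in MIP or S-index therefore cannot be derived.

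**The case against.** The strongest reply is that 3–4 was meant as a ceiling: progress when the load is no harder than that. The default sentence does not exclude this, since it only negates whatever the condition means. Two features of section 3.7 favour it. The sentence opens with weekly progression, and the next hold, for persistent symptoms, is a tolerability hold. This stands as a plausible account of intent. It does not rescue the wording, which gives a two-sided band and says nothing about ratings below it. Another possible intent, 3–4 as a target zone, would also move a participant below 3 upward.

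It may also be said that the article condenses a fuller protocol and cites sources that are not shown. That would answer a complaint about missing detail. Here a trigger and an explicit default are both stated, and the fault lies in how they are set.

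Three stronger readings are tempting, and the documents do not support them:

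- *Ratings below 3 will be common.* Section 3.6.1 uses a similar format before testing: "a warm-up session (one set of 30 breaths at 40% of S-index) has been included". But that load is a share of S-index, not MIP, and the article does not say that it feels easy. No Borg rating is reported at any load, so the warm-up shows nothing about frequency.
- *The trial will be under-dosed and lose power.* This needs the frequency and the dose-response, and neither is given. The abstract itself describes the experimental treatment as loading at 40% of MIP, without mentioning progression, so a held participant still receives the dose named there.
- *The comparison is compromised.* It is not. The rule is part of the treatment as randomised, and a held load remains well above the 7 cmH2O sham: 24/7 = 3.4, 32/7 = 4.6 and 40/7 = 5.7 times, at the assumed MIP values.

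**Conclusion.** The point holds as a minor fault in a stated rule. As worded, a participant rating below 3 is held at the current load for as long as that rating lasts, just like one rating above 4, against the weekly progression that section 3.7 itself announces. The size that can be stated is the withheld step: 10% of initial MIP, or 25% of the starting load at the first decision. Only if the rating stays below 3 throughout would the load be unchanged for all 36 sessions. The cmH2O values and the relative intensities rest on assumed MIP levels and gains and illustrate the rule only.

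Some dilution of the effect on MIP and S-index is possible, but its amount is unknown. The intended rule may well have been 4 or less; the text leaves that open.

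**What to change.** Replace the trigger and its default in section 3.7 with:

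> Increase the load by 10% of initial MIP if the end-of-week Borg rating is 4 or less and reflux symptoms are not persistent; in all other cases keep the load unchanged.

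This retains the step size, the hold above 4 and the symptom hold. It needs no extra visits, measurements or participants, and section 3.7 already requires a diary that tracks the progression of training.

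The cost is procedural. Section 5 says that the approved study is closed to modification, and a changed dosing trigger is an amendment. It should be submitted to the Ethics Committee as a minor amendment, or as a clarification if the authors can confirm that 4 or less was what was approved.

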### 3.8. Methods of Data Collection

Data collection, both prior to and following the intervention, will be conducted by the principal researcher. The moderation of these procedures will be done by the main researchers’ supervising professor.

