### 3.4. Randomization and Blinding Procedures

The allocation concealment will be ensured through the randomization process. Sealed, opaque envelopes will be used, numbered consecutively by an Assistant Professor of the Laboratory of Advanced Physiotherapy, University of West Attica, who will not participate in any other process of the study. Participant assignment will be concealed from both participants and evaluators, while the principal investigator will be informed, in accordance with a single-blinding procedure.

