We should also bear in mind the introduction of a novel IMT technique supported by electronic devices, such as the K5 system. This technique presents further advantages in training over the threshold IMT. Thus, the study may further emphasize the clinical relevance of diaphragmatic strengthening, particularly considering the documented reduction in respiratory muscle strength among individuals with GERD [46]. Additionally, the combined use of objective clinical measurements and disease-specific questionnaires is expected to provide deeper insight into the interaction between GERD and respiratory function. The present study protocol adheres to established methodological standards, including appropriate randomization procedures, concealed allocation, examiner blinding, and justified sample size calculation, thereby enhancing the internal validity and reliability of the findings.

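### Evaluator blinding is claimed but contradicted: Section 3.8 gives data collection to the principal researcher, and nothing says that the assessor of MIP and S-index is blinded

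*Protocol article*

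**What the plan says.** Four places in the protocol article bear on who measures the outcomes and what that person knows.

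- **Section 3.4 (Randomization and Blinding Procedures):** "Participant assignment will be concealed from both participants and evaluators, while the principal investigator will be informed, in accordance with a single-blinding procedure".
- **Section 3.6 (Outcome Measurements):** "A trained physiotherapist will perform: (a) MIP (Micro RPM), according to ERS statement". The same physiotherapist measures the S-index and administers the RDQ and Reflux-Qual. For spirometry: "This will be performed by a pulmonologist with adequate training".
- **Section 3.8 (Methods of Data Collection):** "Data collection, both prior to and following the intervention, will be conducted by the principal researcher". The only oversight named is: "The moderation of these procedures will be done by the main researchers’ supervising professor".
- **Section 7 (Discussion)** lists among the trial's methodological strengths "concealed allocation, examiner blinding, and justified sample size calculation".

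Section 3.6.1 makes inspiratory muscle strength the primary outcome, measured by MIP and S-index. It describes the S-index as ten maneuvers during which the participant is encouraged to give a maximum effort.

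**The concern.** Section 3.4 names one role that knows the allocation. Section 3.8 gives data collection before and after the intervention to what appears to be that role. If 3.8 is followed literally, the person collecting the outcomes is not blinded, and the claims in 3.4 and the Discussion are wrong.

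This matters more here than it would for a laboratory value. MIP and S-index record what the participant can be brought to produce on the day, and encouragement from the tester is part of the S-index procedure. A tester who knows the arm could press harder, or accept more attempts, in one arm than in the other. The sham device addresses participant expectation, not the tester's behavior. No later analysis can separate such a bias from a training effect.

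**Working it through.** The question is who assesses, so the text decides it and no figure does. The arithmetic in step 4 only shows how much a bias of a given size would matter.

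**1. Who knows the arm, and who measures**

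| Section | Role named | Task | Stated to be blinded? |
|---|---|---|---|
| 3.4 | Evaluators | Not specified | Yes |
| 3.4 | Principal investigator | Not specified | No, informed of allocation |
| 3.6 | Trained physiotherapist | MIP, S-index, RDQ, Reflux-Qual | Not stated here |
| 3.6 | Pulmonologist | Spirometry | Not stated here |
| 3.8 | Principal researcher | Data collection before and after the intervention | Not stated here |
| 7 | Examiner | Not specified | Yes |

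**2. Are the principal researcher and the principal investigator the same person?** The article never equates the two terms. Section 3.8 pairs the principal researcher with a supervising professor. Section 6.2 limits data access to the principal investigator, the supervisor and the statistician. The matching pairs make sameness the natural reading, but it remains an inference.

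**3. Can the sections be reconciled as they stand?** Two readings are open.

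- *Collection means performing the measurements.* Then 3.8 conflicts with the evaluator blinding in 3.4 and 7. It also conflicts with 3.6 for spirometry and, unless the physiotherapist is the principal researcher, for MIP and S-index.
- *Collection means gathering completed records.* Then the physiotherapist of 3.6 could be a separate, blinded evaluator and 3.4 could hold. The article does not say so.

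**4. Illustration of size**

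The article's sample size comes first, as a check on the scale. With d = 1.3, power 0.80 and two-sided alpha 0.05 (sidedness assumed), the noncentral t gives 10.34, so 11 per arm and 22 in total. This matches Section 3.5. Power at 11 per arm is 0.826.

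Now assume no true effect and a differential tester bias of b SD favoring the IMT arm, with a two-sided two-sample t test. The noncentrality is b × √(n/2) on 2n − 2 degrees of freedom. For example, n = 15 and b = 0.3 give 0.3 × √7.5 = 0.82, and the rejection rate is 12.5%.

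| Assumed bias (SD) | 11 per arm (22 in 3.5) | 15 per arm (30 in the abstract) |
|---|---|---|
| 0 | 5% | 5% |
| 0.1 | 5.6% | 5.8% |
| 0.2 | 7.3% | 8.3% |
| 0.3 | 10.3% | 12.5% |
| 0.5 | 20.1% | 26.2% |

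The planned analysis in Section 4 is the group-by-time interaction of a 2 × 3 repeated-measures ANOVA. For a bias at T2 only, and assuming compound symmetry with correlation r between visits, the noncentrality is n × b² / [3(1 − r)] on 2 and 4(n − 1) degrees of freedom. With n = 12 and r = 0.7 (both assumed):

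- b = 0.3: 12 × 0.09 / 0.9 = 1.20, rejection about 14%
- b = 0.5: 12 × 0.25 / 0.9 = 3.33, rejection about 33%

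The direction is the same under the planned test. The level depends on r, which the article does not give.

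**The case against.** The strongest reply is that blinding is stated twice and put in doubt only by a two-sentence section. Section 3.6, which is the section on measurement, names a physiotherapist and a pulmonologist. Section 3.8 stands directly before Data Management and may concern only the gathering of records. It cannot mean that the principal researcher performs every measurement, because spirometry belongs to the pulmonologist. The two role titles are not equated. The only text on encouragement concerns the S-index; MIP is measured by device under cited guidance. The assumed biases have no source in the article.

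Much of this stands. A reader might infer that evaluator blinding does not exist, or that detection bias has been shown. The documents support neither. That conclusion needs two inferences: that the two titles mean one person, and that this person conducts the tests. The first is likely; the second is open. The false-positive rates are illustrations, and at 0.1 SD the inflation is negligible. Spirometry is less directly affected.

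The reply does not remove the contradiction. Section 3.6 does not call the physiotherapist blinded or separate from the principal investigator, and moderation by a supervisor is not blinding. Nor is this detail that a condensed article may leave out: the article does say who collects the data, and that statement conflicts with its own blinding claim. MIP is also a maximal voluntary effort, so it is plausibly open to the same influence even though encouragement is not described for it.

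**Conclusion.** The point holds as a contradiction that must be resolved before outcomes are assessed. Evaluator blinding is claimed in 3.4 and 7, but 3.8 contradicts it and 3.6 does not secure it. The conclusion rests on reading the principal researcher as the principal investigator. Whether the tester will in fact be unblinded cannot be settled from the article.

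The problem falls on both primary outcomes. Its size is unknown. Under the two-sample t test, the false-positive rate would be about 6% for an assumed bias of 0.1 SD, 10–13% for 0.3 SD and 20–26% for 0.5 SD. These figures show that a moderate bias would matter in a trial this small; they do not estimate one.

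**What to change.** Reconcile Sections 3.4, 3.6, 3.8 and 7. In 3.8, state that:

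- MIP, S-index, MEP, RDQ and Reflux-Qual at T1, T2 and T3 are collected only by the physiotherapist of 3.6;
- this person is not the principal investigator, delivers no training, and has no access to the allocation, the training diary or the device load (the load differs by arm and would reveal it);
- the principal investigator only handles completed records and is not present at testing.

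If the physiotherapist of 3.6 is the principal investigator, withdraw the evaluator-blinding claims in 3.4 and 7 and describe the trial as participant-blinded only.

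**Cost.** If the physiotherapist is a separate person, the change is wording and a rota rule, with no new staff and less scheduling flexibility. If the two are the same person, withdrawing the claim needs no resources but leaves a less favorable blinding statement; keeping evaluator blinding would require another assessor. Section 5 says that no further modifications are allowed after ethics approval, so the sponsor should settle with the committee how the clarification is recorded.
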